## Abstract

To assess the efficacy of different modalities and frequencies of physical exercise on glycaemic control in adults with prediabetes. A two-phase, parallel, randomised, controlled clinical trial will be carried out, in 210 participants. In phase 1, 120 participants will be randomized into four arms: (1) aerobic exercise, (2) aerobic exercise combined with resistance, (3) high-intensity intervallic exercise and (4) control group. In phase 2, 90 new participants will be randomized into three arms, using the exercise modality that showed the best glycaemic control in phase 1 in the following manner: (1) frequency of 5 days/week, (2) frequency of 3 days/week and (3) frequency of 2 days/week. The control group (n = 30) will be included in phase 1 to evaluate the effect of any type of intervention versus no intervention. Data collection will be performed at baseline and after 15 weeks of follow up. Sociodemographic data, medication, comorbidity, blood biochemical parameters, blood pressure, anthropometric measurements, body composition, physical activity, sedentary lifestyle, diet, smoking, alcohol consumption, quality of life and sleep questionnaires will be collected. Physical activity, sedentary behaviour and sleep will be further determined with an accelerometer, and continuous glycaemia will be determined with a glycaemic monitor, both during seven days, at two time points. The main dependent variable will be the reduction in the mean amplitude of glycaemic excursions. The impact of these interventions on health will also be evaluated through gene expression analysis in peripheral blood cells. The results of this study will contribute to a better understanding of the mechanisms behind the glucose response to physical exercise in a population with prediabetes as well as improve physical exercise prescriptions for diabetes prevention. Increasing glycaemic control in people with prediabetes through physical exercise offers an opportunity to prevent diabetes and reduce associated comorbidities and health costs.

## 1. Introduction

Type 2 diabetes mellitus (T2D) is a highly prevalent chronic disease causing significant complications that reduce the quality of life and life expectancy [1]. Type 2 diabetes also represents a considerable economic burden for health systems and society and has become one of the major worldwide public health problems. In addition, T2D and its risk factors (obesity, diet and physical inactivity) affect the most socially vulnerable population to a greater extent, contributing to social inequalities in health [2].

The development of T2D is gradual and preceded by a prediabetic state [3]. The American Diabetes Association (ADA) defines prediabetes as fasting plasma glucose (FPG) levels between 100 and 125 mg/dL, and/or a glucose tolerance test (GTT) after 2 h between 140 and 199 mg/dL, and/or glycated haemoglobin (HbA1c) levels between 5.7 and 6.4% [3]. The International Diabetes Federation (IDF) estimated that 7.5% of the population worldwide aged 20–79 years has prediabetes [2]. However, the prevalence in the Spanish population is close to 14% [4]. Furthermore, an ADA expert panel estimated that 70% of the population with prediabetes will develop T2D in the future [5], with an annual incidence of 5–10% [6]. Nevertheless, prediabetes can revert to normoglycaemia, especially with the implementation of lifestyle interventions [7,8]. For the population with prediabetes, a lifestyle modification focused on a healthy diet [9] and physical activity (PA) promotion [10] is the cornerstone of prevention [7].

Most studies evaluating different exercise modalities and frequencies use only point measures such as HbA1c, FPG or other indicators of glucose metabolism [11,12,13]. The mean amplitude of glycaemic excursions (MAGE) and percentage of time in range (TIR) are careful measures of glycaemic control obtained by continuous glucose monitoring (CGM) [14]. Fluctuations in blood glucose levels during the day likely carry greater health risks than FPG levels or HbA1c [15]. Several studies suggest that physical exercise reduces the postprandial glucose response [16,17] and reduces the MAGE [18]. However, few studies have examined the effect of exercise on glycaemic variability using CGM (24 h/d) [19,20].

In addition to more classical approaches, transcriptomic analysis in blood cells is increasingly used for clinical purposes to identify early risk biomarkers of different pathologies, including T2D [21]. Peripheral blood cells (PBC), which include the peripheral blood mononuclear cell (PBMC) fraction, can express almost the entire genome and mimic gene expression profiles of internal organs and tissues [22]. These cells can reflect metabolic alterations related to increased adiposity and/or obesity early on, as well as metabolic recovery after a weight-loss intervention [23]. Moreover, PBMC transcriptomic profile is affected by exercise [24]. For all these reasons, these blood cells are an interesting non-invasive biological source of biomarkers of the impact of exercise on homeostatic glucose control.

Current evidence shows that preventive interventions focused on lifestyle modification (PA and diet) are efficient in clinical practice with the prediabetic population [25]. According to the World Health Organization (WHO) recommendations, between 150–300 min of physical exercise per week should be accumulated [26], but it is unknown what time distribution is most beneficial for preventing T2D. Furthermore, there are few studies comparing the effect of different modalities of physical exercise (such as aerobic or resistance) on glycaemic control and none have adequate sample sizes to allow generalisability of their results [27]. Some studies on the effect of different modalities and frequencies on visceral adipose tissue (VAT) reduction suggest that aerobic training (AT) should be practiced 3 days/week, with 30–60 min per session. In the case of high-intensity interval training (HIIT), even sessions of less than 30 min would achieve sufficient energy expenditure to produce effects [28].

Physical activity can be classified into four dimensions: modality, frequency, duration and intensity. Modality is the type of PA performed (aerobic, anaerobic, resistance or balance); frequency refers to the number of sessions/day or week; duration refers to the amount of time (minutes or hours) spent performing PA; and intensity is an indicator of metabolic demand of the activity. The higher the intensity, the greater the effort required to perform the activity. Intensity can be quantified objectively with physiological measurements (i.e., heart rate or oxygen consumption), measured subjectively (i.e., talk test or Borg scale) or quantified by body movements (i.e., body accelerations in three axes) [29].

Aerobic training is characterised by training at an intensity that allows the aerobic route to be used for obtaining energy, in which the body’s large muscles move rhythmically for a sustained period of time. Aerobic training has been associated with glucose control and improvement in insulin sensitivity [30]. This type of exercise can also be called aerobic activity or endurance activity and improves cardiorespiratory fitness. Some examples of AT are running, brisk walking, swimming or cycling [26].

Interval training (IT) is a modality of physical training that consists of short periods of exercise of varying intensity with short periods of rest in between. This modality of exercise strategy is associated with glycogen depletion, which may induce improvements in insulin sensitivity [31]. High-intensity interval training is a type of interval training that is performed at high intensity. It is a very vigorous physical activity, with a heart rate ≥85% or a VO_2_Max ≥60% [32], performed in short bursts interspersed with breaks [33]. There is a consensus regarding the decrease in training time in the HIIT exercise modality [19,28,34]; because it is a vigorous activity, 75 min/week is recommended, instead of 150 min/week in the case of moderate activities [26].

Resistance training (RT), also referred to as muscle strengthening, is defined as the exercise performed against some type of resistance to increase muscle strength, muscle endurance or muscle power. Resistance training exercises can be performed by weightlifting using machine weights, free weights or elastic bands that resist movement. Some examples of RT are bench press, seated row, shoulder press, leg press, or weight strength [35]. Resistance training regimens should include multi-joint exercises that affect more than one muscle group (i.e., lower back extension, chest press, shoulder press, pull-down, dips, leg press or squats) and involve major muscle groups, such as quadriceps extensions, leg curls, biceps curls and triceps extensions [36,37]. Research findings show that this intervention strategy increases insulin sensitivity and glucose tolerance primarily through increased skeletal muscle mass [37].

Although numerous studies have shown the beneficial effects of physical exercise on glycaemic control in people with prediabetes [19,38,39], there are few studies comparing different modalities of physical exercise (i.e., AT, RT, IT). Furthermore, none of the studies conducted included an adequate sample size to generalise the results [11,27]. One study that compared moderate AT and HIIT reported greater benefits of AT on body mass index (BMI) and body fat, whereas similar results were obtained from both modalities for FPG and HbA1c [11]. Another study, also conducted on people with prediabetes, concludes that both RT and AT lead to a decrease in insulin resistance. However, maximal RT reported a greater increase in glucose uptake capacity (in muscles), whereas AT showed a greater ability to increase insulin sensitivity, which supports the recommendation to combine maximal RT with AT to prevent the progression of prediabetes to T2D [27].

In summary, although there is a wide amount of evidence showing the beneficial effects of PA on health, and particularly, on the prevention of T2D, there is no clear consensus on the specific type of exercise to be prescribed to achieve the maximum benefits. This project aims to explore different types of exercise and different frequencies, to understand their impact on glucose homeostatic control, by using new technological approaches.

Most studies agree that interventions of at least 12 weeks should be carried out to assess changes in blood glucose, with a training frequency of 3 days/week [12,13,38,40]. Likewise, HbA1c reflects the mean glucose concentration over the previous 8–12 weeks [41]. This experimental study has been designed to evaluate the effect of different modalities and frequencies of physical exercise in participants with prediabetes at 15 weeks of follow-up, considering in all the experimental groups the amount of time recommended by WHO.

Furthermore, this project will use CGM, which will provide us with very accurate data on glycaemic variability throughout the day and relate them to daily activity data (PA and sedentary behaviour (SB), sleep, diet intake, among others), allowing us to determine new factors involved in glycaemic control that may suggest new forms of intervention in prediabetes.

## 2. Objectives

### 2.1. Main Aim

The main aim of the present study is to compare the efficacy of three modalities (Phase 1) plus control group and three different frequencies (Phase 2) of physical exercise on MAGE in adults with prediabetes.

### 2.2. Secondary Aim

The secondary aims are to evaluate the effect of different physical exercise modalities and frequencies on the following variables: FPG, glycaemic variability measured continuously (24 h), normalization of glycaemic values (reversal), BMI, body composition (percentage and grams of total fat mass and muscle mass), visceral adipose tissue (VAT) waist circumference, lipid profile, inflammation markers, blood pressure, sleep duration and quality and transcriptomic markers of metabolic health assessed in PBC.

## 3. Experimental Design

### 3.1. Design

The GLYCEX study (GLYcaemic Control with EXercise) is a randomised, parallel, phase II clinical trial with three active arms in each of the two phases plus a control group in the first phase. The intervention groups will receive a supervised exercise intervention for 15 weeks in both phases. The control group will receive general recommendations of PA, based on WHO recommendations, and after 15 weeks, will be invited to participate in the second phase of the study. Baseline evaluations will be repeated after 15 weeks.

Study interventions were reported using the Template for Intervention Description and Replication (TIDieR) as a reference [42] (Supplementary Material Table S1). The present protocol was elaborated following the Standard Protocol Items: Recommendations for Intervention Trials (SPIRIT) 2013 Statement [43]. Reporting of the study will follow the CONSORT statement recommendations on RCTs [44]. Table 1 summarizes all items included in the trial registry, as suggested by the World Health Organization (WHO, 2018).

### 3.2. Participants

Participants’ identification and recruitment will be carried out at different primary care centres from Mallorca, Spain, that formally agree to participate in this project, and through posters distributed at different points of interest, such as hospitals, universities, primary care centres and patient associations. Likewise, it will also be disseminated through social networks, such as Twitter. Interested patients will receive the information sheet, sign the written informed consent and eligibility criteria will be verified.

Inclusion criteria: Adults aged 18–65 years, with overweight or obesity (BMI >25 and <35 Kg/m^2^), inactive (<150 min PA/week) and with prediabetes (fasting blood glucose 100–126 mg/dL), and who have signed the informed consent will be included.

Exclusion criteria: People with uncontrolled hypertension, diagnosis of T2D or oral anti-diabetic prescription, active cancer, terminal illness or cognitive impairment, pregnancy, cardiovascular disease, inability to perform moderate-vigorous physical exercise for the next 3 months, major surgery or hospital admission in the last 3 months, haematological disease that interferes with HbA1c determination, presence of any condition (medical, psychological, social or geographical) current or anticipated that limits participation in the study, or participation in another clinical trial will be excluded.

### 3.3. Sample Size and Randomization

The sample size has been calculated to detect significant differences in MAGE of at least 1.5 mg/dL and considering a standard deviation of 1.4 mg/dL [45] in any of the three modalities and a dropout rate of 20%, so 30 subjects will be needed in each group, with a sample of 180 participants, 90 in each phase. Furthermore, a control group (30 patients) will be added to evaluate the effect of any type of monitored exercise in these patients versus usual clinical practice. Randomization will be carried out by permuted blocks of eight in a 1:1:1:1 ratio and stratified by prognostic factors: gender, age and obesity using the open-source Oxford Minimization and Randomization (OxMaR) program [46].

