#### 4.3.2. Glycaemic Variability

The continuous blood glucose monitoring system (Dexcom G6, Dexcom Inc., San Diego, CA, USA) [61] will be used to assess glycaemic variability for 14 consecutive days in all samples [62]. The sensor will be placed at V−1 and removed after 14 days. It will be placed again at the beginning of week 14 and removed at V1. The Dexcom G6 sensor will be inserted into the subcutaneous adipose tissue in the lower abdomen (below the umbilicus) [19,63]. To optimise the usefulness of continuous glycaemic monitoring, participants will be asked to keep an electronic diary (e-diary), where they will record the food intake, the timing of intakes and the time they go to sleep and wake up during 14 consecutive days. Mean amplitude of glycaemic excursions and time in range (TIR) will be estimated from the 14-day sensor glucose profiles. Mean amplitude of glycaemic excursions will be calculated by taking the mean of the increases or decreases in blood glucose (from nadirs to peaks or vice versa) when the rising and falling segments exceed the 1 standard deviation blood glucose value over a 24 h measurement period [14].

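### The MAGE difference of 1.5 mg/dL and SD of 1.4 mg/dL behind the sample size look far too small, possibly through a unit error, and need checking before the trial's sensitivity is claimed

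*Protocol article*

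**What the plan says.** Protocol article, section 3.3 (Sample Size and Randomization), sets out to "detect significant differences in MAGE of at least 1.5 mg/dL and considering a standard deviation of 1.4 mg/dL" (the SD is attributed to reference 45), and allows for "a dropout rate of 20%, so 30 subjects will be needed in each group". The total is given as "with a sample of 180 participants, 90 in each phase", and 30 controls are then added. The section names neither the power nor the comparison that was sized, and does not say whether the SD is that of the MAGE level, of its change, or of the baseline-adjusted residual.

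Section 5.1 makes change in MAGE at 15 weeks the primary outcome. Section 5.3 analyses it by ANOVA/GLM adjusted for baseline, at the 0.05 level. Section 4.3.2 counts a swing towards MAGE only "when the rising and falling segments exceed the 1 standard deviation blood glucose value over a 24 h measurement period".

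The article gives no mean, range or SD for MAGE other than the 1.4. Its nearest figures are the diagnostic ranges in the Introduction: "fasting plasma glucose (FPG) levels between 100 and 125 mg/dL, and/or a glucose tolerance test (GTT) after 2 h between 140 and 199 mg/dL". Section 3.2 enrols on fasting glucose of 100–126 mg/dL alone.

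**The concern.** MAGE discards small fluctuations by construction, so it lies on the scale of a person's larger daily swings. Someone between the article's fasting and 2 h cut-offs rises by tens of mg/dL after a glucose load. Read as the SD of the MAGE level, 1.4 mg/dL would put about 95% of participants inside a band of 2 × 1.96 × 1.4 = 5.5 mg/dL (normal approximation). That is hard to square with swings of that size differing between people.

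The two inputs are the only justification given for 30 per arm. If the SD is understated while the difference is right, the trial is far less sensitive than stated, and a null result could be misread as excluding differences above 1.5 mg/dL. If both carry the wrong unit, the size is as intended but the stated sensitivity is wrong by the conversion factor. Section 4.1.2 also takes the best-performing phase 1 modality into phase 2, so overstated sensitivity would flatter the reliability of that choice.

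**Working it through.** **Inputs.** Difference 1.5 mg/dL, SD 1.4 mg/dL, dropout 20% (section 3.3); alpha 0.05 (section 5.3), taken as two-sided. Power is not stated, so it is varied.

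**1. Reproducing 30 per arm.** Standardised difference: 1.5/1.4 = 1.071. Evaluable n is rounded up, divided by 0.8, and rounded up again.

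| Method | Evaluable n per arm | Enrolled per arm |
|---|---|---|
| Two-sample t-test, 80% power | 14.7 → 15 | 15/0.8 → 19 |
| Two-sample t-test, 90% | 19.3 → 20 | 20/0.8 = 25 |
| Two-sample t-test, 95% | 23.65 → 24 | 24/0.8 = 30 |
| Three-group F-test, 90% (extreme means 1.5 apart, third midway) | 23.1 → 24 | 24/0.8 = 30 |

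A Bonferroni correction for three pairwise tests at 90% power (normal approximation) also gives 24 and 30. The stated size therefore follows from the stated inputs by more than one standard route, and the text does not say which was used.

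**2. The scale implied by the article's cut-offs.** A person inside both diagnostic ranges rises by between 140 − 125 = 15 and 199 − 100 = 99 mg/dL. Purely as an illustration, values spread over that span would have an SD of about (99 − 15)/4 = 21 mg/dL, or 84/√12 = 24 mg/dL if uniform. Neither is a figure from the article, and neither is an estimate of the SD of MAGE.

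**3. Could change scores or baseline adjustment bring the SD down to 1.4?** The residual SD after adjustment is SD × √(1 − r²), so r = √(1 − (1.4/SD)²). For assumed raw SDs of 5, 10 and 20 mg/dL, the baseline-to-week-15 correlation would have to be 0.96, 0.990 and 0.998. For a change score, SD × √(2(1 − r)) = 1.4 gives r = 1 − 1.96/(2 × SD²), which is again 0.96, 0.990 and 0.998. Correlations that high are unlikely for free-living monitoring 15 weeks apart with an exercise programme in between.

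**4. Sensitivity with 24 completers per arm** (pairwise t-test, two-sided 0.05). The difference detectable at 80% power is 0.826 × SD. All SDs other than 1.4 are assumptions.

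| Analysis SD (mg/dL) | Power for 1.5 mg/dL | Detectable at 80% power (mg/dL) |
|---|---|---|
| 1.4 | 95% | 1.2 |
| 2 | 72% | 1.7 |
| 3 | 40% | 2.5 |
| 5 | 17% | 4.1 |
| 10 | 8% | 8.3 |

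The largest SD that keeps 80% power for 1.5 mg/dL is 1.5/0.826 = 1.8 mg/dL.

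**5. If both inputs were mmol/L** (assumption; factor 18). 1.5 × 18 = 27 mg/dL and 1.4 × 18 = 25 mg/dL. The ratio stays 1.071 and n per arm is unchanged. Only the stated target difference moves, from 1.5 to about 27 mg/dL.

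**The case against.** The strongest reply is that nothing in the article contradicts an SD of 1.4 mg/dL. The cut-offs are diagnostic limits for single glucose values, joined by and/or, so pairing them as one person's trajectory is a construction. Enrolment uses fasting glucose alone, so a participant's 2 h value may be normal, and the 15–99 mg/dL span does not describe the trial population. A single rise after a glucose load is also not MAGE, which here is averaged over 14-day profiles. The analysis works on change or a baseline-adjusted residual, whose SD can be smaller than that of the level. Finally, the figure has a cited source that cannot be consulted here.

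All of this stands as a limit on the inference. It does not remove the doubt: the cut-offs still point to excursions of tens of mg/dL, and step 3 shows how extreme the correlation would have to be.

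Two stronger readings are tempting and should not be made. A reader might infer that the trial cannot deliver its stated sensitivity. With the inputs as printed, pairwise power is 95%, and the loss of power depends on SDs that are assumed. A reader might also infer that 30 per arm is reached only by choosing 95% power for unadjusted pairwise tests. The three-group F-test, which is the planned type of analysis, gives the same number at 90%. Unstated power alone would carry little weight, since a fuller protocol may state it.

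**Conclusion.** The concern holds as serious doubt about two inputs, not as an error of arithmetic or a proven contradiction. Both 1.5 and 1.4 mg/dL look far too small for MAGE as the article defines it, and a unit slip is a possible but unproven explanation. The margin is thin: an analysis SD above about 1.8 mg/dL takes power for 1.5 mg/dL below 80%, so no particular large SD is needed for the statement to fail. At an assumed SD of 5 mg/dL power is 17%, and at 10 mg/dL it is 8%. These figures assume 24 completers per arm, two-sided 0.05 and one unadjusted pairwise comparison. Under the mmol/L explanation the trial is sized as intended, and only the stated target is wrong, by a factor of 18. Either way, the difference of 1.5 mg/dL should not be relied on until the inputs are confirmed.

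**What to change.** Revise the sample size paragraph in section 3.3:

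- Check the unit of both figures against reference 45, and establish whether the SD is of the MAGE level, its change, or the baseline-adjusted residual. Correct the figures accordingly and print both in mg/dL.
- Name the power and the comparison that was sized (overall F-test and number of groups, or a given pair).
- Keep 30 per arm, and state in mg/dL what 24 completers per arm can detect: about 0.83 SD for a pairwise comparison at 80% power. If the SD remains uncertain, show this over a range of SDs.

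This changes one paragraph and adds no participants. The price is that the stated detectable difference is likely to become less favourable.
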